We will sequentially recruit and enroll eligible women for all specific aims. There will be three separate consent forms (Appendix A, B and L). Screening and informed consent for participation in the studies involving VIA or VILI, colposcopy and specimen collection (S.A. 1, 2 and 3) will take place in a private gynecologic exam room prior to pelvic exam. Because satisfactory visual exam or clinical evidence of cervical or pelvic infection will only become evident after exam, participant numbers will be assigned after VIA and colposcopy. Women who are unsure about enrollment and would like time to consider will be given an information sheet (Appendix C) and may return for enrollment at a later date. VIA in these women will be deferred until their next visit. Eligibility and informed consent for the post-LEEP genital shedding sub-study will take place at a clinical visit, prior to their LEEP procedure. Women will be given an information sheet specific to this part of the study, in addition to the normal clinical materials in use that explain the LEEP procedure (Appendix D).

Statistical Considerations and Sample Size Calculation

**Specific Aim 1:** To calculate a sensitivity of 75% with a confidence interval of 5% in both directions and a two-sided alpha of .05, we will need to complete sequential VIA and colposcopy in ***1800* women**.^83^

To determine a specificity of 80%, with a confidence interval of 5% in both directions and a two-sided alpha of .05, we calculate that we will need to examine 400 women. Because the scientific outcome of specificity is most important, we will use the estimate of 1,800 women (900 VIA and 900 VILI to account for laboratory and sampling error) to power our study.

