Data Storage: The study will be conducted within the existing clinic settings in the Nyanza Province. Data will be collected from the electronic medical record and on study-specific forms (Appendices F and G). Study data will be included as part of the patient’s medical file and maintained in locked file cabinets within the clinic. Data will be abstracted to computers by data entry clerks and managed by the assigned data manager at each site. Abstracted data will be labeled by unique study ID only. A file correlating study ID and medical file number will be kept in separate password-protected Excel computer file and accessible only to the core research team. Additionally, all study computers are password protected and kept in locked offices within the clinics.

Statistical Analysis:

Statistical analysis for all specific aims will be carried out using STATA and SPSS software.

**Specific Aim 1**: The goal of specific aim 1 is to calculate the sensitivity, specificity and predictive values of VIA and VILI for CIN2/3, with colposcopy as the gold standard. Colposcopy will be performed on every participant, regardless of screening result, to avoid verification bias.^92^ To calculate the sample size for this study, we assume that the prevalence of CIN2/3 among HIV-infected women at FACES will be 7%, as has been seen in the cervical cancer screening program at FACES.^78^ Sample size calculations will be based on prior estimates of VIA sensitivity, as these are more prevalent and therefore have more precision.

Sensitivity: Previous studies have shown that VIA has a sensitivity of 60-86%^39, 40, 91, 93-97^ for detection of CIN2/3 among healthy women, which is comparable to the sensitivity of cervical cytology and would be an acceptable test characteristic for this setting. In order to determine sensitivity, we will construct a 2 x 2 table, and divide the number of women with a true positive VIA result (i.e. those with disease diagnosed by colposcopy and VIA) by the number of true positive VIAs plus the number of false negative VIAs. Specificity: Specificity values for VIA range from 64 to 94% for the detection of CIN2/3.^39, 40, 91, 98, 99^ To determine specificity of VIA, we will divide the number of participants with true negative VIA (i.e. has no disease diagnosed colposcopically) by the number of true negative tests plus the number of false positive tests.

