In addition to sensitivity and specificity, we will calculate the positive and negative predictive values of VIA. Studies have shown a PPV of VIA for CIN2/3 to range from 9-27% in HIV-negative women.^97, 100, 101^ To calculate the PPV in our study, we will divide the number of participants with a positive VIA by the number of participants found to have CIN2/3 on biopsy. VIA has been shown to have a negative predictive value (NPV) of 91-99.5% in HIV-negative women.^102^ To calculate the NPV, we will divide the number of participants with a negative VIA by the number of participants with no evidence of disease at colposcopy, either by visual impression or a negative biopsy result. Confidence limits for estimates of sensitivity, specificity, PPV and NPV will be exact, based on the binomial distribution.

Finally, we will compare the test characteristics between the two screening modalities using a McNemar’s test of proportions.

**Specific Aim 2**: To determine the cut-off value for the p16^INK4a^ biochemical assay that will provide the highest sensitivity and specificity for the detection of CIN2/3, we will construct a Receiver Operating Characteristic (ROC) curves using the results of the ELISA-based assay and the histology specimens. An ROC curve will allow us to plot the True Positive Rate (TPR) and the False Positive Rate (FPR) for various values of the p16^INK4a^ assay. As TPR is equivalent to the sensitivity of a test, and 1-FPR is the specificity, the graphical representation, as well as the calculated Area Under the Curve will allow us to determine the cut-off value for p16^INK4a^ to define a “positive test” with the highest sensitivity and specificity.

We will compare the absolute differences in sensitivity and specificity for detection of CIN2/3 of p16^INK4a^ and HR-HPV using the Mann-Whitney U test. The values of p16^INK4a^ will be determined from the ROC curves in Specific Aim 2. The sensitivity and specificity of the HR-HPV tests will be calculated as below:

- To calculate **sensitivity**, we will divide the number of women with a true positive test by the number of true positives plus the number of false negative HR-HPV testing.
- To calculate **specificity**, we will divide the number of participants with no disease diagnosed colposcopically (true negatives) by the number of true negative plus false positive HR-HPV tests.

Confidence limits for estimates of sensitivity and specificity will be exact, based on the binomial distribution.

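### As written, the Aim 1 formulas for PPV and NPV divide test-result totals by disease totals, so they do not define predictive values

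*Protocol*

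**What the plan says.** Aim 1 (Protocol, Objectives) names four quantities for VIA and VILI: sensitivity, specificity, PPV and NPV. The formulas are in Data Quality and Management, Statistical Analysis, Specific Aim 1.

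- Sensitivity and specificity of VIA are defined correctly there, from a 2 x 2 table.
- For PPV: "we will divide the number of participants with a positive VIA by the number of participants found to have CIN2/3 on biopsy".
- For NPV: "we will divide the number of participants with a negative VIA by the number of participants with no evidence of disease at colposcopy", where absence of disease may rest on visual impression or on a negative biopsy.
- Exact binomial confidence limits are planned for all four quantities.
- As published benchmarks in HIV-negative women, the section cites a PPV of 9-27% and an NPV of 91-99.5%.

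The protocol gives no other definition of PPV or NPV.

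**The concern.** A predictive value conditions on the test result: of the women who test positive (or negative), what share do (or do not) have CIN2/3? The denominator must be a test-result total, and the numerator must be the correctly classified women within it. The written formulas fail on both counts. Their denominators are all women with CIN2/3 and all women without disease, and their numerators include the misclassified women.

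Both quantities are named in Aim 1, and they are what a clinic would use to tell a screened woman what her result means. The written PPV exceeds 1 whenever false positives outnumber false negatives, which is expected at low prevalence, and such a figure would stand out. The written NPV is harder to spot because it can look credible. A reported 81.9% would suggest that about 18% of VIA-negative women have CIN2/3, when about 2% would be expected.

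**Working it through.** The protocol states no expected PPV or NPV for this study, so there is no planned figure to reproduce. The check applies the written and the standard formulas to one expected 2 x 2 table.

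**Inputs**
- Prevalence, from the Specific Aim 1 analysis text: "the prevalence of CIN2/3 among HIV-infected women at FACES will be 7"%.
- Sensitivity, from the sample size section: "To calculate a sensitivity of 75% with a confidence interval of 5% in both directions".
- Specificity, from the same section: "To determine a specificity of 80%, with a confidence interval of 5% in both directions".
- Women per test: "900 VIA and 900 VILI to account for laboratory and sampling error". The ratios below do not depend on this number.
- Ranges for sensitivity: "Previous studies have shown that VIA has a sensitivity of 60-86"%; and for specificity, 64-94% (Specific Aim 1 analysis text).
- Assumption: 'no evidence of disease' means no CIN2/3.

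**Expected table for 900 women having VIA**
- CIN2/3: 900 x 0.07 = 63. No CIN2/3: 900 - 63 = 837.
- TP = 0.75 x 63 = 47.25; FN = 63 - 47.25 = 15.75.
- TN = 0.80 x 837 = 669.6; FP = 837 - 669.6 = 167.4.
- VIA positive = 47.25 + 167.4 = 214.65; VIA negative = 669.6 + 15.75 = 685.35.

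**Results at the planning values**

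| Quantity | Formula as written | Result | Standard formula | Result |
| --- | --- | --- | --- | --- |
| PPV | (TP+FP)/(TP+FN) = 214.65/63 | 3.41 | TP/(TP+FP) = 47.25/214.65 | 22.0% |
| NPV | (TN+FN)/(TN+FP) = 685.35/837 | 81.9% | TN/(TN+FN) = 669.6/685.35 | 97.7% |

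The standard results fall inside the protocol's cited benchmarks (9-27% and 91-99.5%). The written results fall outside both.

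**Range at 7% prevalence.** The written formulas reduce to:
- written PPV = sensitivity + (1 - specificity) x 0.93/0.07
- written NPV = specificity + (1 - sensitivity) x 0.07/0.93

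| Quantity | Lowest (sensitivity, specificity) | Highest (sensitivity, specificity) |
| --- | --- | --- |
| Written PPV | 1.40 (60%, 94%) | 5.64 (86%, 64%) |
| Written NPV | 65.1% (86%, 64%) | 97.0% (60%, 94%) |
| Standard PPV | 11.2% (60%, 64%) | 51.9% (86%, 94%) |
| Standard NPV | 95.5% (60%, 64%) | 98.9% (86%, 94%) |

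The written PPV is above 1 throughout. The written NPV happens to come close to the standard one in one corner (sensitivity 60%, specificity 94%: 97.0% against 96.9%), but that is coincidence.

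**Other prevalence.** At an assumed 16%, with 144 cases and 756 non-cases, the written formulas give 259.2/144 = 1.80 and 640.8/756 = 84.8%. The standard ones give 108/259.2 = 41.7% and 604.8/640.8 = 94.4%. The fault does not depend on the 7%.

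**Confidence limits.** An exact binomial interval needs a count of successes within a fixed number of trials. For the written PPV the count exceeds the number of trials (214.65 against 63), so no interval exists. For the written NPV the numerator contains 15.75 false negatives who are not in the denominator. Software would return limits, but they would not be valid.

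**The case against.** **The intent is recoverable.** The same section specifies a 2 x 2 table, defines sensitivity and specificity correctly, cites plausible benchmarks and asks for binomial limits. A competent analyst using standard software would probably produce the right values, and an analysis plan that is not at hand may define them properly. This stands in part: a reader might infer that the study would publish a PPV of 3.4, and the protocol does not support that prediction. The figures show only what the text yields if followed literally. The text is still an explicit wrong rule, not a detail left open.

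**A kinder reading of the numerators.** Taking them as true positives and true negatives does not help. The formulas then become sensitivity (47.25/63 = 75%) and specificity (669.6/837 = 80%), which are already defined.

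**The formulas are upside down.** A reader might call them inverted. They are not: reciprocals would be 214.65/47.25 = 4.54 and 685.35/669.6 = 1.02. They are ratios of margins.

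**HR-HPV specificity.** A reader might see the same fault in the Aim 2 text, "divide the number of participants with no disease diagnosed colposcopically (true negatives) by the number of true negative plus false positive HR-HPV tests", and conclude that specificity would always be 100%, since all women without disease equal true negatives plus false positives. That reading has to discard the label in the numerator. With the label the formula is TN/(TN+FP), which is correct. The same loose gloss accompanies the correct VIA specificity formula.

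**Importance.** A reader might infer that PPV decides whether a see-and-treat programme overtreats. The protocol does not go that far. The Background ties overtreatment to the false positive rate, and the sample size section treats specificity as the most important outcome. The VIA specificity formula is sound.

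**Conclusion.** The point holds for PPV and NPV. Both definitions are wrong as written, and nothing else in the protocol corrects them. Followed literally at 7% prevalence, 75% sensitivity and 80% specificity, they give 3.41 instead of 22.0% and 81.9% instead of 97.7%. The exact figures rest on those planning values and on reading 'no disease' as no CIN2/3. That the formulas are not predictive values rests on neither.

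This is a drafting error in two definitions of named Aim 1 quantities. It leaves the data, the sample size and the sensitivity and specificity formulas untouched, and it does not threaten the validity of the study. It needs correcting because one resulting figure would be impossible and the other could pass unnoticed.

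**What to change.** Replace the two sentences in the Specific Aim 1 analysis text, for VIA and for VILI, with:

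- PPV: women with a positive test and CIN2/3, divided by all women with a positive test.
- NPV: women with a negative test and no CIN2/3, divided by all women with a negative test.

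The planned exact binomial limits then apply as stated, with the test-positive and test-negative totals as the numbers of trials.

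The change should not be extended to p16 or HR-HPV. Aims 2a and 2b name only sensitivity and specificity. The Aim 2 sample is also enriched: 140 women with positive and 60 with negative colposcopy, and 57% of the positives expected to have CIN2/3. That is 0.57 x 140 = 79.8, or about 40% of 200 (taking none among the negatives), against 7% in the clinic. Raw predictive values from that sample would not describe screening performance.

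The cost is two sentences before analysis, with no effect on participants, data collection or sample size.

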**OBJECTIVES:**

General:

We seek to establish the link between the presence, diagnosis and treatment of cervical dysplasia and HIV genital shedding. We also seek to establish the sensitivity and specificity of three resource-appropriate screening methods, VIA, VILI and p16^INK4a^ biomarker testing, for cervical dysplasia.

Specific (Aims):

**Aim 1:** **To calculate the sensitivity, specificity, and the positive and negative predictive values of visual inspection of the cervix after application of 3-5% acetic acid (VIA) and visual inspection with Lugol’s Iodine (VILI) for the diagnosis of cervical intraepithelial neoplasia grade 2 and grade 3 (CIN2/3) in HIV-infected women.** HIV-infected women enrolled in care at the FACES clinics in western Kenya will undergo VIA or VILI and colposcopy with directed biopsy as indicated. The colposcopy will be used as the reference standard, allowing for calculation of sensitivity, specificity, positive and negative predictive value of VIA and VILI.

Hypothesis 1: VIA and VILI will have test characteristics validating their use as a screening test for cervical dysplasia among HIV-infected women in resource-limited settings.

**Aim 2: To define the quantitative value of a biochemical assay for p16^INK4a^ that predicts cervical neoplasia with the greatest sensitivity and specificity among HIV-infected women using a receiving operating characteristic (ROC) curve.**

**Aim 2a: To compare the sensitivity and specificity of the p16^INK4a^ biochemical assay with that of HR-HPV testing.** HIV-infected women enrolled in care at the FACES clinics in western Kenya will undergo specimen testing for p16^INK4a^ and HR-HPV, followed by colposcopy with directed biopsy as indicated.

**Aim 2b: To calculate the sensitivity and specificity of the p16^INK4a^ biochemical assay for the detection of CIN2/3 using colposcopy as the gold standard.** HIV-infected women will have p16^INK4a^ specimens collected prior to colposcopy. Diagnosis for positive p16 will be based on the ROC curve cut-off determined in the pilot study, with colposcopy as the reference standard as above.

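### Aim 1's PPV and NPV formulas are wrong as written: at the protocol's own inputs they give 341% and 81.9%, where the true predictive values are 22.0% and 97.7%.

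*Protocol*

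**What the plan says.** Aim 1 (Protocol, Objectives) promises four accuracy measures for each visual test, with colposcopy as the reference standard "allowing for calculation of sensitivity, specificity, positive and negative predictive value of VIA and VILI". It gives no formulas there.

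The formulas are in Data Quality and Management, Statistical Analysis, Specific Aim 1. Sensitivity and specificity are defined correctly, from true and false positives and negatives in a 2 x 2 table. The predictive values are not defined in that way:

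- PPV: "we will divide the number of participants with a positive VIA by the number of participants found to have CIN2/3 on biopsy".
- NPV: "we will divide the number of participants with a negative VIA by the number of participants with no evidence of disease at colposcopy", where absence of disease rests on visual impression or a negative biopsy.

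The same paragraph cites comparison ranges from HIV-negative women (PPV 9-27%, NPV 91-99.5%). It then fixes the interval method: "Confidence limits for estimates of sensitivity, specificity, PPV and NPV will be exact, based on the binomial distribution".

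**The concern.** PPV is the share of test-positive women who have CIN2/3. NPV is the share of test-negative women who do not. Each needs a joint count in the numerator and a test-result total in the denominator. The protocol puts a test-result total in the numerator and a disease-status total in the denominator, and uses no joint count at all. The first quantity is therefore the ratio of VIA-positive women to women with CIN2/3, which is not a proportion and can exceed 1. The second is the ratio of VIA-negative women to women without disease.

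Two of Aim 1's four named outputs would be wrong if the text were followed, and could not be compared with the ranges cited beside them. PPV also bears on the overtreatment worry raised in the Background, since it tells a see-and-treat programme what share of screen-positive women have the target lesion.

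**Working it through.** **Inputs, all from the protocol**

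- Sensitivity (Se) 75%: "To calculate a sensitivity of 75% with a confidence interval of 5% in both directions and a two-sided alpha of .05" (sample size, Specific Aim 1).
- Specificity (Sp) 80%: "To determine a specificity of 80%, with a confidence interval of 5% in both directions and a two-sided alpha of .05" (same place).
- Prevalence of CIN2/3 (p) 7% (Statistical Analysis, Specific Aim 1).
- Women having VIA, N = 900: "900 VIA and 900 VILI to account for laboratory and sampling error". N cancels out of every ratio below.

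The protocol states no expected PPV or NPV for this study, so there is no planned figure to reproduce.

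**Expected 2 x 2 table**

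- Women with CIN2/3: 900 x 0.07 = 63. Women without: 837.
- True positives (TP): 63 x 0.75 = 47.25. False negatives (FN): 15.75.
- True negatives (TN): 837 x 0.80 = 669.6. False positives (FP): 167.4.
- VIA-positive: 47.25 + 167.4 = 214.65. VIA-negative: 669.6 + 15.75 = 685.35.

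**Written and correct formulas**

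| Measure | As written | Result | Correct | Result |
| --- | --- | --- | --- | --- |
| PPV | (TP+FP)/(TP+FN) = 214.65/63 | 341% | TP/(TP+FP) = 47.25/214.65 | 22.0% |
| NPV | (TN+FN)/(TN+FP) = 685.35/837 | 81.9% | TN/(TN+FN) = 669.6/685.35 | 97.7% |

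The correct values lie inside the protocol's cited ranges (9-27% and 91-99.5%). The written ones lie outside both.

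**Across the cited accuracy ranges** (Se 60-86%, Sp 64-94%, p = 7%, all combinations)

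The written ratios can be rearranged to show how they behave:

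- Written PPV = Se + (1 - Sp)(1 - p)/p. Minimum, at Se 60% and Sp 94%: 0.60 + 0.06 x 0.93/0.07 = 140%. Maximum, at Se 86% and Sp 64%: 0.86 + 0.36 x 0.93/0.07 = 564%. It is always above 100%.
- Written NPV = Sp + (1 - Se)p/(1 - p). Minimum, at Se 86% and Sp 64%: 0.64 + 0.14 x 0.07/0.93 = 65%. Maximum, at Se 60% and Sp 94%: 0.94 + 0.40 x 0.07/0.93 = 97%. It is specificity plus a small amount.
- The correct formulas give PPV 11-52% and NPV 95.5-98.9% over the same combinations.

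**Could another reading rescue the text?**

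- If each numerator is limited to women in the stated denominator, the formulas return sensitivity (47.25/63 = 75%) and specificity (669.6/837 = 80%), which are already defined.
- If each fraction is inverted, they give 63/214.65 = 29% and 837/685.35 = 122%.

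Neither reading yields a predictive value.

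**Interval method**

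Exact binomial limits need the numerator to be a subset of the denominator. For the written PPV, 214.65 out of 63 has no such limits. For the written NPV, software would return limits for 685 out of 837, but they would be invalid because the 15.75 false negatives in the numerator are not among the 837.

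**The case against.** The best defence is that the error is harmless in practice. PPV and NPV are standard quantities. The protocol calls for a 2 x 2 table, defines sensitivity and specificity correctly, and cites realistic comparison ranges. An analyst who obtained a PPV of 341% would see the mistake at once. The Aim 1 sample size rests on sensitivity and specificity, so enrolment and precision planning are untouched. The Background's overtreatment remark also speaks of the false positive rate, which specificity addresses directly.

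Most of this is fair, but it concerns consequences and leaves the formulas wrong. It also protects PPV better than NPV. A written NPV of 65-97% is a believable number and at high specificity falls inside the cited 91-99.5%, so nothing would alert the analyst. The overtreatment question does not rest on PPV alone, though PPV remains relevant to it. A correct statistical analysis plan may exist, but this is not detail left to such a plan: the protocol states the estimators, and states them wrongly.

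One side issue is better called unclear than wrong. The NPV sentence does not say whether a biopsy showing CIN1 counts as negative. Since the target is CIN2/3, it may be meant to. The figure of 837 above counts every woman without CIN2/3, including any with CIN1.

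**Conclusion.** The concern holds. Both predictive-value formulas are wrong as written, and no other part of the protocol corrects them. At the planning inputs the PPV is overstated by a factor of about 15 (341% against 22.0%), and the NPV is understated by about 16 percentage points (81.9% against 97.7%). These sizes rest on the planned 7% prevalence, 75% sensitivity and 80% specificity and will differ in the real data. The formula error does not depend on them. The conflict with the exact binomial intervals is outright for PPV; for NPV the danger is a plausible but wrong figure.

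**What to change.** Replace the two sentences in Statistical Analysis, Specific Aim 1, with:

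- PPV: the number of women with a positive test and CIN2/3 by the reference standard, divided by the number of women with a positive test.
- NPV: the number of women with a negative test and no CIN2/3 by the reference standard (normal colposcopy, negative biopsy, or biopsy showing CIN1), divided by the number of women with a negative test.

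State that both apply separately to VIA and VILI, since the present sentences name VIA only while Aim 1 promises both. The exact binomial limits can then stand as planned. The cost is two sentences of protocol text, with no change to procedures, data collection or sample size.

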**ABSTRACT**

Cervical cancer and HIV are intersecting epidemics that both disproportionately affect low-income women; the impact of the socioeconomic disparity and biologic synergy of these two diseases is seen dramatically in Kenya, where cervical cancer is the most common cancer killer. HIV-infected women are at increased risk for the development of cervical precancer and cancer, develop more aggressive lesions and are affected at younger ages. Although screening for and treatment of precancer has reduced the incidence of cervical cancer to close to zero in resource-rich countries, strategies are costly and not available in most resource-limited countries. Novel testing and treatment methods that can be carried out in low-resource settings are urgently needed to prevent cervical cancer in these settings, especially among HIV-infected women. Using a cross-sectional study design, we propose to test two potentially low-cost and effective cervical cancer screening methods: **visual inspection with acetic acid** (VIA) and **protein biomarkers** expressed in the presence of cervical dysplasia, neither of which have been well-studied in HIV-infected women. We will also randomize a small subset of women to undergo VIA compared to **Visual Inspection with Lugol's Iodine (VILI**) to compare the test characteristics of these two screening exams. In addition, remarkably little is known about the potential **impact of the presence, diagnosis and treatment of HPV-related dysplasia on HIV genital shedding, a major risk factor for HIV transmission**. To explore the impact of the presence, diagnosis and treatment of HPV-related cervical dysplasia on HIV-1 in genital secretions, we will compare the levels of HIV-1 RNA found in the cervicovaginal secretions of women with no evidence of cervical dysplasia to levels in women with high-grade cervical dysplasia. We will also compare the levels of HIV-1 RNA prior to and after cervical biopsy as well as up to 14 weeks after standard treatment for cervical dysplasia using loop electrosurgical excision procedure (LEEP). Results from this study will inform the prioritization and design of safe, effective and low-cost cervical cancer screening and prevention programs for HIV-infected women in resource-limited settings.

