We propose a ***cross-sectional*** study to evaluate this specific aim. Each participant will undergo a VIA or VILI with specimen collection for p16^INK4a^ and HR-HPV and colposcopy by a different clinician during a single clinic visit. The study clinician performing the colposcopy will be blinded to the results of the VIA or VILI. For women in the VILI arm, the colposcopy will be performed first in order to eliminate any interference with colposcopy interpretation from the iodine staining. Biopsy decisions will be made at the time of colposcopy, but deferred until after the VILI. Any woman with cervical lesions suspicious for dysplasia seen at the time of colposcopy will undergo biopsy. Colposcopy will be used as the reference standard for presence or absence of CIN2/3, with biopsy results being the final diagnosis when available. Women with a normal colposcopy without biopsy will be considered to have no disease.Specific Aims 1, 2, 2a and 2b)

We propose a **prospective cohort** study using a subset of women identified from the cross-sectional study in Specific Aims 1 and 2a to evaluate specific aim 2c during a one-year follow-up visit. We will recruit women for this follow-up study who participated in the pilot p16^INK4a^ ELISA study (Aim 2a) and had normal colposcopy or CIN1. In a single visit, each participant will undergo a VIA with specimen collection for p16^INK4a^ and HR-HPV followed by colposcopy and biopsy if needed.

We propose a ***case-control*** study to measure and compare the presence and quantity of HIV-1 RNA in the cervicovaginal specimens of women with biopsy-confirmed CIN2/3 (cases) and age-matched women without evidence of cervical disease as measured by negative VIA (controls). We will compute the odds ratio for HIV-1 detection and compare log transformed mean viral loads between cases and controls. (Specific Aim 3)

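### The tests named for the two accuracy comparisons do not fit the data: McNemar for VIA versus VILI in different women, Mann-Whitney for p16 versus HR-HPV in the same women, the latter at a p16 cut-off tuned on those women

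*Protocol*

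**What the plan says.** **VIA versus VILI.** Under Statistical Analysis, the Aim 1 text opens: "The goal of specific aim 1 is to calculate the sensitivity, specificity and predictive values of VIA and VILI for CIN2/3". It closes: "Finally, we will compare the test characteristics between the two screening modalities using a McNemar’s test of proportions". Study Design gives each woman one visual test: "Each participant will undergo a VIA or VILI with specimen collection for" the p16 and HR-HPV assays. The Aim 1 sample size splits the 1,800 women as "900 VIA and 900 VILI to account for laboratory and sampling error", and the Abstract speaks of randomising women between the two tests ("We will also randomize a small subset of women to undergo VIA compared to" VILI).

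**p16 versus HR-HPV.** For Aim 2a the protocol will compare absolute differences in sensitivity and specificity between p16 and "HR-HPV using the Mann-Whitney U test". Study Procedures describes a single cervical swab for both assays, and Data Quality and Management says HR-HPV is run on fluid from the p16 vial.

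**Cut-offs.** In that comparison the p16 values "will be determined from the ROC curves in Specific Aim 2", at the threshold giving the highest sensitivity and specificity. The wording of Aim 2b places this threshold in the pilot study, and Study Design labels the pilot ELISA study as Aim 2a. HR-HPV positivity is fixed in advance at a ratio of 1.00. Aim 2b then applies the pilot cut-off to the larger sample, for p16 alone.

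**The concern.** The two tests are in effect the wrong way round. McNemar's test counts discordant pairs within the same woman, and the VIA/VILI design yields none. Mann-Whitney compares two independent samples, and the p16/HR-HPV data are paired. These are the only tests the protocol names for the Aim 1 comparison and for the claim in Hypothesis 2 that p16 beats HR-HPV. If they stay, the analyst must choose a replacement for the first after seeing the data, and will run the second with a variance that does not match the design.

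The cut-off is a separate problem. A threshold picked for best performance in a sample looks better there than it will elsewhere. HR-HPV gets no such tuning, so the Aim 2a contrast leans toward p16.

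**Working it through.** The protocol gives no sample size, effect size or power for either comparison, so there is no stated figure to reproduce. The check matches each test to its data and then sizes the consequences.

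**1. VIA versus VILI.** McNemar's statistic is (b − c)²/(b + c), where b and c count women positive on one test and negative on the other. No woman has both tests, so b and c do not exist.

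What the design can support is a two-sample comparison. At the protocol's 7% prevalence, each group of 900 has 0.07 × 900 = 63 expected CIN2/3 cases and 837 women without. With m = 63, p1 = 0.75 (the protocol's planning sensitivity), p̄ the mean of p1 and p2, and two-sided alpha 0.05:

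power = Φ{[Δ − 1.96√(2p̄(1−p̄)/m)] / √([p1(1−p1) + p2(1−p2)]/m)}

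- p2 = 0.85: (0.10 − 0.1397)/0.0707 = −0.56, power 29%.
- p2 = 0.90: (0.15 − 0.1327)/0.0664 = 0.26, power 60%.
- 80% power needs about 18 points (0.75 against 0.93).

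The alternatives p2 are illustrative.

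**2. p16 versus HR-HPV: effect of ignoring the pairing.** Planned cases: 140 positive colposcopies × 57% ≈ 80 CIN2/3. Assumed, not in the protocol: sensitivities of 85% and 95%, and a within-woman correlation φ.

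- Unpaired SE = √[(0.85×0.15 + 0.95×0.05)/80] = √(0.175/80) = 0.0468.
- Paired SE = √[(0.175 − 2φ√(0.1275×0.0475))/80] = √[(0.175 − 0.1556φ)/80].
- Power = Φ(0.10/SE − 1.96), which is 57% with the unpaired SE.

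| φ | Paired SE | Unpaired/paired SE | Paired power |
|---|---|---|---|
| −0.1 | 0.0488 | 0.96 | 54% |
| 0 | 0.0468 | 1.00 | 57% |
| 0.3 | 0.0400 | 1.17 | 70% |
| 0.5 | 0.0349 | 1.34 | 82% |

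These margins allow φ no lower than about −0.1. A simulation of the named rank test on paired 0/1 results (20,000 runs, 80 cases, both sensitivities 0.80) agrees. Its type I error at a nominal 5% is 7.1% at φ = −0.2, 5.3% at 0, 3.0% at 0.2, 1.3% at 0.4 and 0.7% at 0.5. McNemar stays between 4.8% and 5.6%.

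**3. Tuned cut-off.** The simulation draws normal scores in women with and without CIN2/3, picks the cut-off maximising sensitivity + specificity in the sample, and subtracts the true performance at that cut-off. Assumed: 80 cases and true AUC 0.90 to 0.75. For women without CIN2/3 there are two sources: the plan (200 − 80 = 120) and the pilot counts reported in the Aim 2c sample size (55 CIN1 + 190 normal = 245).

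| Cases / non-cases | Optimism, AUC 0.90 | Optimism, AUC 0.75 |
|---|---|---|
| 80 / 120 | 0.046 | 0.061 |
| 80 / 245 | 0.039 | 0.055 |

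A repeat run agreed to within 0.002. With 80 and 120, truly equal tests and HR-HPV simulated as independent of p16, a correctly paired test on sensitivity + specificity favours p16 falsely in about 6% of trials, against a nominal 2.5%. With a pre-fixed cut-off the rate is 2.5% to 2.6%.

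**The case against.** **The two modalities might be VIA and p16.** The Abstract does call VIA and biomarkers the two methods under test, and McNemar would suit that pair. But the sentence closes the Aim 1 analysis, whose stated goal is VIA and VILI, and stands before the Aim 2 text. This reading does not hold.

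**Aim 1 survives.** A reader might infer that the McNemar error undermines the VIA and VILI accuracy estimates. It does not. Aim 1's goal is to estimate each test's accuracy, and the exact binomial limits planned for each are untouched. Only the contrast between them is affected.

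**Both p16 faults might seem to push toward a false win for p16.** They do not. Positive correlation is plausible for two HPV-related markers from one swab, and then ignoring the pairing is conservative, so the harm is lost power. Only negative correlation reverses this. The tuned cut-off does favour p16, but the two effects are different in kind and cannot be relied on to cancel.

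**p16 accuracy might seem to be reported only in the tuning sample.** That is not so. Aim 2b carries the pilot cut-off to the larger sample, which is a real, partial safeguard. What stands is narrower: Aim 2b covers p16 alone, the comparison with HR-HPV is not repeated there, and exclusion of pilot women is not stated.

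**The sizes in steps 2 and 3 rest on assumptions.** They do, hence the ranges. The mismatch between test and design needs none of them.

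**Conclusion.** The point holds on all three parts, with different weight.

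- **VIA versus VILI:** a plain error. The named test cannot be computed, whatever is assumed.
- **p16 versus HR-HPV test:** also a plain error, usually conservative. With 80 cases and assumed sensitivities of 85% and 95%, the SE is 0% to 34% too wide for φ from 0 to 0.5, and power is 57% against 57% to 82% paired. Under negative correlation the direction reverses.
- **Cut-off:** a modest bias toward p16, confined to the Aim 2a comparison. Optimism in sensitivity + specificity is about 0.045 to 0.06 with the planned 120 women without CIN2/3, and about 0.04 to 0.055 with the 245 reported, for true AUC 0.90 to 0.75. The pilot's CIN2/3 count is not reported, so 80 cases is itself an assumption.

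A reader might also infer that both assay results will exist for all 1,800 women. The documents support less. Specimens are planned for every participant, but the protocol does not clearly commit to running HR-HPV on all of them, and the budget has no line for it.

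**What to change.** 1. **VIA versus VILI:** replace McNemar with a two-sample chi-square or Fisher test and a confidence interval for the difference, separately in women with CIN2/3 (sensitivity) and without (specificity).
2. **p16 versus HR-HPV:** replace Mann-Whitney with exact McNemar and a confidence interval for the paired difference, again separately in women with and without CIN2/3.
3. **Cut-off:** lock the pilot p16 cut-off and make the comparison in Aim 1/2b women who were not in the pilot and have both assay results. If HR-HPV is not assayed in them, keep the comparison in the pilot and correct it for optimism by cross-validation or bootstrap, repeating the cut-off selection in each resample.
4. **Aim 2b:** state that pilot women are excluded.

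The cost is a change of wording in the protocol or analysis plan, made before the comparisons are run. No new participants or specimens are needed. The first option under item 3 does depend on HR-HPV assays being run on stored non-pilot specimens, so the sponsor should confirm whether that is intended.
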